## Abstract

**Background:**

The Masimo Total Hemoglobin SpHb® is a continuous and non-invasive handheld device to measure hemoglobin levels. Previous research has found that SpHb is able to accurately detect hemoglobin levels in adult patients with a similar degree of bias and standard deviation to point-of-care invasive method measurements. Generally, limited clinical evidence, lack of validation of Masimo at higher than and lower than hemoglobin threshold values, and scientific consensus supporting the use of Masimo for accurate hemoglobin testing for the diagnosis of anemia during pregnancy calls for further research.

**Methods and analysis:**

The proposed prospective cohort will be nested within the ongoing Pregnancy Risk and Infant Surveillance and Measurement Alliance (PRISMA) Maternal and Newborn Health (MNH) study. Three study sites (located in Zambia, Kenya, and Pakistan) will participate and collect hemoglobin data at five time points (<20 weeks, 20 weeks, 28 weeks, 36 weeks’ gestation, and six weeks postpartum). We will measure hemoglobin using a venous blood sample via hematology auto-analyzer complete blood count (gold standard) and the non-invasive device. The primary objective is to assess agreement between Masimo total hemoglobin and complete blood count and on a continuous scale using Intraclass Correlation Coefficient and Bland-Altman Analysis. The second objective is to assess agreement between the two measures on a binary scale using Positive Percentage Agreement and Negative Percentage Agreement, Cohen’s Kappa, and McNemar Test. On an ordinal scale, agreement will be measured using Weighted Cohen’s Kappa and Harrel’s Concordance Index. Lastly, we will assess factors that might affect the accuracy of Masimo total hemoglobin using linear mixed models.

**Conclusions:**

The primary aim of this study is to assess the validity of the non-invasive Masimo device compared to the gold standard method of invasive hemoglobin measurements during pregnancy and postpartum periods for the diagnosis of anemia.

## Introduction

### Background

The Masimo Total Hemoglobin SpHb® is a continuous and non-invasive handheld device with an optical sensor placed on the finger that measures hemoglobin levels using pulse oximetry. The measurement takes under one minute and does not require blood samples or laboratory testing. These characteristics make it a particularly promising medical technology for resource-constrained contexts. Previous research studies have found that SpHb is able to accurately detect hemoglobin levels in adult patients with a similar degree of bias and standard deviation to point-of-care (PoC) invasive method (e.g., HemoCue device) measurements, as compared to the gold standard laboratory total hemoglobin complete blood count (CBC) method as a reference
^
1–
3
^. However, other evidence suggests that SpHb test accuracy is limited. A 2015 systematic review of Masimo and HemoCue performance (n=39 studies) found that SpHb had lower precision and wider 95% limits of agreement than PoC
^
4
^. High variability in bias and in limits of agreements for the Masimo device was also found in a study involving pregnant patients
^
5
^. Masimo has been approved by the US Food and Drug Administration (FDA) for use in the general population but has not been approved for use in pregnancy
^
6
^. The general lack of clinical evidence and scientific consensus supporting the use of Masimo for accurate hemoglobin testing for the diagnosis of anemia during pregnancy calls for further research.

### Rationale

The Pregnancy Risk and Infant Surveillance and Measurement Alliance (PRISMA) Maternal and Newborn Health (MNH) study is a population-based, open-cohort study that seeks to evaluate pregnancy risk factors and their associations with adverse pregnancy outcomes, including stillbirth, neonatal mortality and morbidity, and maternal mortality and severe morbidity. The goals are to develop a harmonized data set to improve understanding of pregnancy risk factors, vulnerabilities, and disease burden estimates in sub-Saharan Africa and Southeast Asia. Ultimately, these data will inform development of innovative strategies to optimize pregnancy outcomes for mothers and their newborns.

Anemia, a condition classified as a moderate to severe public health problem in many countries, that affects an estimated 613 million (33%) women of reproductive age worldwide, is a secondary outcome in the PRISMA MNH study
^
7
^. Three current PRISMA MNH study sites additionally conduct non-invasive and continuous hemoglobin monitoring with a Masimo device (located in Kenya, Pakistan, Zambia).

Producing accurate, precise, and comparable hemoglobin measurements is of special importance in pregnancy, both for clinical value in diagnosing anemia and ensuring pregnant women receive appropriate treatment. Additionally, standard of care guidelines for diagnosis of anemia and treatment are not the same across countries even when following WHO’s recommendations
^
8,
9
^. WHO recommends daily oral elemental iron between 30 mg to 60 mg for all pregnant women to meet increased micronutrient requirements in pregnancy and prevent maternal anemia and iron deficiency
^
10
^. In Pakistan and Zambia, standard of care during pregnancy is to prescribe 30-60 mg of elemental iron daily, whereas in Kenya, it is daily dose of 60 mg. In Zambia and Pakistan, if hemoglobin levels are below 11.0 g/dL, daily iron dose is increased to twice or thrice daily, depending on the severity
^
10
^. In Kenya, when hemoglobin levels fall between 5.1 – 8.0 g/dL, women are treated with parenteral iron, but if detected after 36 weeks, a blood transfusion may be necessary
^
11
^. Treatment guidelines for severe anemia vary across these countries. In Pakistan and Zambia, severe anemia is defined as <7.0 g/dL. In Pakistan, severe anemia is treated with IV iron sucrose or IV ferric carboxymaltose administered intravenously, whereas in Zambia it is treated with packed cell or blood transfusion
^
10
^. In Kenya, severe anemia is defined as Hb <5.0 g/dL and is treated with packed cells during pregnancy
^
11
^.

In our study, we will evaluate the compatibility of hemoglobin measurements between SpHb and CBC assessed via five-part autoanalyzer throughout pregnancy and at six weeks postpartum.

### Aim and objectives

The primary aim of this study is to evaluate whether total hemoglobin measures using the Masimo SpHb continuous non-invasive monitoring device are accurate as compared to gold standard CBC laboratory tests using peripheral venous blood samples. To achieve this aim, three statistical objectives were identified:

1.To estimate the level of deviation and agreement between SpHb and CBC values longitudinally.2.To calculate the level of agreement between SpHb and CBC values among binary (healthy versus anemic) and ordinal (mild, moderate, severe anemia versus normal) measures longitudinally.3.To describe sociodemographic and clinical factors affecting the difference between SpHb and CBC values.

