## Methods

### Study design

This proposed study will use a prospective cohort design nested within the ongoing PRISMA MNH open cohort study (see
Figure 1). Three sites currently using Masimo devices will participate: Lusaka, Zambia; Kisumu and Siaya, Kenya; Karachi, Pakistan. Each site has identified defined geographic regions that are appropriate for longitudinal data collection and the conduct of ongoing research involving pregnant women. Hemoglobin measurements for the validation study will occur at five timepoints: <20 weeks, 20 weeks, 28 weeks, 36 weeks’ gestation, and six weeks postpartum. The study sites in Pakistan will also collect measurements at week 32.

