### Objective 1: Deviations/agreement between SpHb and CBC

**
*Intraclass correlation coefficient*
**

The intraclass correlation coefficient (ICC) is a measure of similarity of within-group values in clustered data
^
12
^. Here the ICC (with 95% CI) will be used to evaluate the degree of agreement of hemoglobin values using the degree of variances between SpHb and CBC measurements with respect to variances within SpHb measurements and variances within CBC measurements. Observed ICC with 95% CI will be reported.

**
*Bland–Altman analysis*
**

Bland–Altman (B&A) analysis is a recommended analytical method of assessing the comparability between different techniques/methods using a graphical approach using mean differences and agreement intervals. It will be used to estimate agreement between the two instruments used to measure hemoglobin levels on a continuous scale
^
13,
14
^. The quantification of agreement between two measurements is assessed by determining the mean difference on two quantitative measurements (i.e., the mean difference between the two observers or techniques), their standard deviation and constructing limits of agreement.

Given that multiple repeated measurements are measured on the same participant at different gestational ages, the variances in the ICC and B&A analyses will be calculated according to the data structure. For repeated measures, using the differences between SpHb and CBC measures, both, between variance and within variance will be calculated as follows: 

$$\begin{array}{c} Var(\underline{\delta }\text{.})=\frac{Var_{between}}{n}+\frac{Var_{within}}{n*n_{r}},\\ Var_{between}=\frac{\sum_{i=1}^{n}\;{\left({\underline{\delta }}_{i.}-{\underline{\delta }}_{..}\right)}^{2}}{n-1}\\ {Var}_{\mathrm{within}}=\frac{\sum_{i=1}^{n}\;\sum_{j=1}^{n_{r}}\;{\left(\delta_{ij}-{\underline{\delta }}_{i.}\right)}^{2}}{n(n_{r}-1)} \end{array}$$

Where, subscript
*i* and
*j* denote participant (
*i*) and repeated blood sample (
*j*), where we have
*i*=1,...,
*n* participants and
*j*=1,...,
*n
_r_
* repeated blood samples per participant,
*δ
_ij_
* is the difference between the SpHb and CBC measurements from participant i blood sample j,

*δ
_i_
*
. is the average difference of all repeated samples from participant i,

*δ*
.. is the average difference from all participants and all repeated samples.

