**Positive percentage agreement and negative percentage agreement**

Positive percentage agreement (PPA) and negative percentage agreement (NPA) measure the level of agreement between two sets of binary measures. Here, both PPA and NPA will be used to examine the level of agreement between test methods (SpHb/CBC) in identifying anemia in pregnant women (i.e. anemic/healthy). Bootstrap 95% confidence intervals will be obtained for PPA and NPA based on repeated measurements where observations from the same participant will be sampled or not sampled together.

PPA=#positive(anemia)bySpHb/#positive(anemia)byCBC

NPA=#negative(healthy)bySpHb/#negative(healthy)byCBC

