**Cohen’s kappa**

Cohen’s kappa is a measure of interrater reliability, where 0 indicates agreement equivalent to chance and 1 indicates perfect agreement. For repeated measures of matched pair data, the variance of kappa can be estimated nonparametrically
^
15
^. In this study it will be used to assess the agreement between two procedures (CBC and SpHb) in the independent matched-pair data using defined strata. For example, if both the CBC and SpHb classify a sample as “severe deficiency”, the samples will be rated as “in agreement”. Total number of samples in agreement will be counted and Cohen’s kappa will be calculated as follows:

$$\text{k}=({\text{P}}_{\text{o}}-{\text{P}}_{\text{e}})\text{/}({\text{1-P}}_{\text{e}})$$

Where, P
_o_ is the
*observed* level of agreement and P
_e_ is the
*expected* level of agreement. Here, the observed level of agreement is the proportion of the cases the two techniques agree upon. The expected level of agreement is the proportion of agreement that is expected by change.

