### Objective 3: Factors affecting differences between SpHb and CBC

In order to assess factors that might affect the accuracy of SpHb, we will include the following characteristics in linear mixed models in order to assess differences between paired SpHb and CBC measurements. These variables will be collected during the enrollment visit, ANC visit, and or during the postpartum visit.

Maternal age,Anemia severity stratum,Nutritional status (e.g., iron deficiency),HIV status (Zambia and Kenya sites only),Malaria status (Kenya site only),Helminth infection status (Kenya site only),Gestational age at assessment and at first ANC visit,Technician,Time between SpHb collection and CBC collection,Participant’s early pregnancy BMI (measured at first ANC visit),Mid upper arm circumference (MUAC),Study site,Tobacco use,Estimated plasma volume (PV)
^
17
^ where Kaplan-Hakim formula
^
18
^ estimates PV as: 

PV(cPV)=(1−hematocrit)∗[a+(b∗weightinkg)]

Where,
*a = 1,530* in males and
*864* in females, and

*b = 41* in males and
*47.9* in females.

We will assess differences between these subgroups as follows:

*Candidate forms of the differences in hemoglobin levels (outcome):*

Differences (
*Δ* =
*SpHb*–
*CBC*),Absolute differences |
*Δ*|,Log(SpHb) - log(CBC) = log(SpHb/CBC).

*Comparison of the outcomes across different categories:*

Contingency tables will be constructed where the distribution of the outcome (differences) will be compared across different levels of the risk factors. For example, mean/SD/IQR of the outcome will be listed side by side for each site and p-values using mixed models comparing the distributions between different locations will be reported.

*Plot of the outcome versus risk factors:*

Lowess or kernel smoothing curves will be fitted for the relationship between the outcome and continuous risk factors such as true Hb values.

*Univariate analysis of candidate risk factors:*

One linear mixed model will be fitted for each candidate risk factor. Candidate risk factors will be tested one at a time and marginal associations between the size of measurement errors and each risk factor will be reported as change per sample SD or change w.r.t. reference level, 95% confidence interval and p-values. All effect sizes and CI can be reported in a forest plot

*Multivariate analysis of selected candidate risk factors:*

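### Objectives 1 and 2 promise agreement over time, through pregnancy and postpartum, but the agreement statistics are written only as pooled over visits and no postpartum estimate is fixed

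*Protocol article*

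**What the plan says.** **The promise.** In Aim and objectives, Objective 1 is "To estimate the level of deviation and agreement between SpHb and CBC values longitudinally". Objective 2 asks for binary and ordinal agreement, also longitudinally. The Rationale commits to comparing the two methods "throughout pregnancy and at six weeks postpartum", and the abstract's Conclusions give the primary aim as validity "during pregnancy and postpartum periods for the diagnosis of anemia". Under Study design, "Hemoglobin measurements for the validation study will occur at five timepoints": four antenatal and one postpartum, with a further week-32 visit in Pakistan.

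**The methods for Objectives 1 and 2.**
- Bland-Altman and ICC: the variance formulas centre on a single mean, which "is the average difference from all participants and all repeated samples".
- PPA/NPA: bootstrap intervals "based on repeated measurements where observations from the same participant will be sampled or not sampled together".
- Cohen's kappa: "For repeated measures of matched pair data, the variance of kappa can be estimated nonparametrically". No kappa by visit is stated.
- McNemar: time points are the clusters, and the discordance differences are summed over them into one chi-square.
- Weighted kappa and C-index: the same participant-level bootstrap.

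**Where time does enter.** Objective 3 lists "Gestational age at assessment and at first ANC visit" among the covariates for mixed models of the difference, the absolute difference and the log ratio. Each factor has its own model, and continuous factors get smoothed curves. No visit, period or postpartum term is listed. Under Repeated measures, the sample size section describes agreement at a specific gestational age as an opportunity, given 19 pairs at any one time.

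**The concern.** The objectives ask how agreement behaves over time. In the formulas for Objectives 1 and 2, repeated visits affect only the variance or the interval, and the estimate itself is a single number. If the device's error drifts with gestation, or differs once the woman is no longer pregnant, the headline limits of agreement, ICC, PPA/NPA and kappa are averages over unlike periods. Postpartum readings would also dilute the antenatal result, although the Background names use in pregnancy as the evidence gap.

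The postpartum visit is the weaker spot. The aim names it, but no estimate isolates it. The one listed covariate that places an assessment in time, gestational age, has no natural value six weeks after delivery.

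**Working it through.** **1. The plan's own figure for time-specific agreement.** The sample size section uses 19 pairs per time point, for 90% power at a mean difference of 0.8 SD. A two-sided paired t-test at 0.05 with n = 19 has power 0.909, and 19 is the smallest n reaching 0.90, so the figure reproduces. It concerns detecting a large mean shift. As a basis for estimating agreement it is thin: the 95% half-width at n = 19 is about 0.48 SD for the bias and 0.84 SD for each limit of agreement.

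**2. Precision by visit at the planned size** (900 pairs per site and visit, no attrition).
- Bias: t × SD/√n = 1.963/30 = 0.065 SD.
- Each limit: t × √(1/n + 1.96²/(2(n−1))) = 1.963 × √(1/900 + 3.842/1,798) = 0.112 SD.

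Estimation by visit is therefore well within reach.

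**3. Share of postpartum pairs.** Planned pairs: 2 sites × 900 × 5 + 900 × 6 = 14,400. Postpartum pairs: 3 × 900 = 2,700, or 18.75%, before attrition.

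**4. What pooling can hide.** Every input here is assumed, and none is trial data: CBC mean 11.2 and SD 1.3 g/dL at every visit; difference SD 1.0; cut-off 11.0 throughout; SpHb bias 0.2, 0.4, 0.6 and 0.8 g/dL over the four antenatal visits and 0 postpartum; normal distributions, errors independent of CBC, equal numbers per visit.

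- The article defines PPA as the number positive by SpHb divided by the number positive by CBC.
- P(CBC < 11.0) = Φ(−0.2/1.3) = 0.439.
- SD of SpHb = √(1.3² + 1.0²) = 1.640, so P(SpHb < 11.0) = Φ((−0.2 − bias)/1.640).

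| Visit | Bias (g/dL) | P(SpHb < 11.0) | PPA |
|---|---|---|---|
| <20 weeks | 0.2 | 0.404 | 92% |
| 20 weeks | 0.4 | 0.357 | 81% |
| 28 weeks | 0.6 | 0.313 | 71% |
| 36 weeks | 0.8 | 0.271 | 62% |
| Postpartum | 0 | 0.451 | 103% |
| All pooled | 0.40 | 0.359 | 82% |

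The variance of the five biases is 0.08, so the pooled SD is √(1 + 0.08) = 1.04 against 1.00 within each visit. The width of the pooled limits hardly changes. The antenatal visits alone have a mean bias of 0.50, against 0.40 when postpartum is included.

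**5. Cancellation in McNemar.** Take discordant counts b = (60, 50, 40, 30, 20) and c = (20, 30, 40, 50, 60) over five visits. The differences are 40, 20, 0, −20, −40 and sum to 0. The article's statistic is (4/5) × 0²/4,000 = 0, p = 1, although the visits differ strongly.

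**6. What Objective 3 would still show.** Use the antenatal biases of step 4, take week 15 for the <20-week visit (assumed), and treat errors as independent. The weeks 15, 20, 28 and 36 have mean 24.75 and sum of squares 254.75; the cross-product with bias is 7.1. The slope is 7.1/254.75 = 0.028 g/dL per week, with standard error about 1/√(900 × 254.75) = 0.0021, so z is about 13 at one site. The planned gestational-age model would detect this drift in the mean difference. It would not give PPA or limits of agreement by visit, and it has no term for the postpartum departure.

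**The case against.** **The gestational course is estimated, at least in part.** A reader might infer that the plan leaves change over gestation unexamined. It does not: Objective 3 models and smooths the difference, the absolute difference and the log ratio against gestational age, and step 6 shows that the drift in the illustration would be plain. This stands, and it limits the point to the agreement statistics themselves.

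**Loss of the postpartum pairs is inference.** A reader might infer that all of them drop out. The article gives no coding for gestational age at that visit and says covariates may also be collected postpartum. On any reading, only models containing that covariate are affected. The other univariate models and all Objective 1 and 2 statistics keep the pairs. This stands too.

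**Longitudinally may mean only repeated measures with correct variances, and tables by visit may sit in a fuller plan.** This stands in part. For kappa, weighted kappa and the C-index, pooling is inferred from how variances and intervals are described. For Bland-Altman and McNemar it is written into the formulas, in a section headed Statistical analysis plan, so the mismatch there is stated and not merely condensed. The remark about agreement at specific gestational ages fixes no analysis and does not mention postpartum.

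**The illustration is constructed.** True. The bias path is assumed, and the 11.0 cut-off is applied postpartum for simplicity. It shows that masking is possible, not that it will occur.

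**Conclusion.** The point holds in a limited form. The Objective 1 and 2 statistics are written only as pooled over visits, explicitly for Bland-Altman and McNemar and by implication for the rest, while the objectives and aim speak of agreement over time, in pregnancy and postpartum. Objective 3 covers the gestational course of the mean, absolute and log-ratio difference. Nothing covers the course of limits of agreement, ICC, PPA/NPA or kappa, and no postpartum estimate or period term is fixed.

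Under the assumed inputs, one pooled PPA of 82% would stand for visit values from 62% to 103%, with almost no sign of it in the pooled SD. Up to 18.75% of planned pairs are postpartum and would probably be lost or mis-scaled in models containing gestational age; this rests on that covariate having no natural postpartum value. The matter is an inexpensive improvement that lets the study answer its stated question. It is not a fault that invalidates the design.

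**What to change.** - Objectives 1 and 2: report bias, limits of agreement, ICC, PPA/NPA and kappa by visit (<20, 20, 28 and 36 weeks, and six weeks postpartum), with week 32 for Pakistan only.
- Give one pooled antenatal summary and report postpartum separately from it. Keep the participant-level bootstrap and the repeated-measures variances for the pooled figures.
- Objective 3: add a categorical visit or period term, or a pregnant/postpartum indicator with gestational age nested within pregnancy, so that postpartum pairs stay in the model. State how gestational age is coded at the postpartum visit.

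**Cost.** Changes of wording and extra tables, with no new data. Visit-specific intervals are somewhat wider than pooled ones, with the half-widths of step 2 at 900 per site; attrition would widen them further.

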## Methods

### Study design

This proposed study will use a prospective cohort design nested within the ongoing PRISMA MNH open cohort study (see
Figure 1). Three sites currently using Masimo devices will participate: Lusaka, Zambia; Kisumu and Siaya, Kenya; Karachi, Pakistan. Each site has identified defined geographic regions that are appropriate for longitudinal data collection and the conduct of ongoing research involving pregnant women. Hemoglobin measurements for the validation study will occur at five timepoints: <20 weeks, 20 weeks, 28 weeks, 36 weeks’ gestation, and six weeks postpartum. The study sites in Pakistan will also collect measurements at week 32.

